### Secondary endpoints

We will report the proportion of men with post-biopsy SAEs (see table “Secondary endpoints”) by study arm, where applicable.

### Sample size calculations

Original sample size calculation (performed in March 2017)

#### *Basic data and assumptions used in the sample size calculations*

We used data from the STHLM3 trial for sample size calculations. In this data, 18% of men with PSA  $\geq 3$  had a clinically significant prostate cancer when biopsied with SBx. We further

noted that  $rTPF=1.25$  for clinically significant prostate cancer comparing MRI+TBx with SBx based on the results from a meta-analysis (Schoots et al. 2015). We set the noninferiority delta to 4 percentage points for demonstrating noninferiority with respect to sensitivity of clinically significant prostate cancer. We set the alpha to 0.025.

#### *Primary contrast*

This study was originally powered for the contrast of Strategy 6 vs 1. Simulating 1000 trials (by bootstrapping from the STHLM3 data) under the assumptions outlined in the preceding section 303 men need to be biopsied in the SBx arm based on  $PSA \geq 3$  to have 80% power to demonstrate non-inferior sensitivity of S3M+MRI+TBx compared with PSA+SBx. This means that at least 415 men need to be biopsied in the SBx arm (since some men are not randomized based on  $PSA \geq 3$  but on  $S3M \geq 11\%$ ) and, consequently, 623 to the MRI arm (because of the 2:3 randomization). Total number of men undergoing workup according to protocol (SBx in the no MRI arm and MRI and TBx if PI-RADS  $\geq 3$  in the MRI arm) is thus 1038. Assuming 20% dropout, 1300 men need to be randomized.

#### *Updated sample size calculations (performed during Spring and Summer 2019)*

We revised the sample size calculations above in order to have sufficient statistical power to answer comparisons of Stockholm3 vs. PSA within the experimental arm.

The updated, final sample size is the result of a balance between time and financial constraints on one hand and the need to maximise the power for contrasting Strategies 6 vs. 3 on the other hand. In fact, different assumptions about the joint probability of  $ISUP \geq 2$  and screening positive on the PSA test [ $Pr(ISUP \geq 2, PSA \geq 3 \text{ ng/ml})$ ] and about the TPF of the PSA test [ $Pr(PSA \geq 3 \text{ ng/ml} | ISUP \geq 2)$ ] lead to different required sample sizes.

Based on the sample size calculation, we decided to increase the number of men invited into the study to ~50000. Based on an updated estimate of the expected participation rate (25%), this will lead to ~12500 men included in the study and to ~2100 randomised men based on PSA or Stockholm3 (assuming ~16.5% of the enrolled men will test positive on either screening test; 13% passed on PSA alone, leading to ~1600 randomized men with  $PSA \geq 3 \text{ ng/ml}$ ), ~1700 of whom will complete the diagnostic chain, assuming a 20% drop-out rate.

The updated sample size will give:

1. 50–90% power for the contrast S3M+TBx+SBx versus PSA+TBx+SBx. This is based on the following assumptions: 0.015–0.03 probability of detecting  $ISUP \geq 2$  and screening positive on the PSA test (Grönberg et al. 2015), 0.57–0.63 TPF for the PSA test (Thompson et al. 2005),  $rTPF$  (Stockholm3  $\geq 11\%$  vs  $PSA \geq 3$ ) equal to 1 (Grönberg et al. 2015), and a conservative DDR estimate (Alonzo, Pepe, and Moskowitz 2002). The non-inferiority margin was set to  $\delta = -\log(0.78)$  and alpha to 0.025.

Note: the contrast S3M+TBx+SBx versus PSA+TBx+SBx is nested within the experimental study arm, where about 7500 men will be included (due to the 2:3 randomisation). We further assumed a 20% drop-out rate, leading to 6000 men available for the analyses.

| DR_psa | TPR_psa | power |
|--------|---------|-------|
| 0.015  | 0.57    | 0.48  |
| 0.020  | 0.57    | 0.60  |
| 0.025  | 0.57    | 0.70  |
| 0.030  | 0.57    | 0.77  |
| 0.015  | 0.59    | 0.52  |
| 0.020  | 0.59    | 0.64  |
| 0.025  | 0.59    | 0.73  |
| 0.030  | 0.59    | 0.81  |

|       |      |      |
|-------|------|------|
| 0.015 | 0.61 | 0.55 |
| 0.020 | 0.61 | 0.67 |
| 0.025 | 0.61 | 0.77 |
| 0.030 | 0.61 | 0.84 |
| 0.015 | 0.63 | 0.59 |
| 0.020 | 0.63 | 0.71 |
| 0.025 | 0.63 | 0.80 |
| 0.030 | 0.63 | 0.87 |

2. More than 90% power for the contrast PSA+MRI+TBx+SBx vs PSA+SBx (rDP = 1.3, noninferiority margin for  $\Delta DP \delta = 0.04$ ,  $\alpha = 0.025$ ).

Thus, contrast 1 drives the required samples size of the study. We therefore powered the study (with respect to sample size for sending out invitations and enrolling participants) to have sufficient statistical power to answer comparisons of Stockholm3 vs. PSA within the experimental arm.

Note: no correction for multiple comparisons was made. This means that each of the three tests (with respect to the ISUP 2, ISUP 1, and biopsy endpoints) has an approximate type I error rate of 2.5% if the corresponding null hypothesis is true. If all three null hypotheses are true and we assume the tests to be independent, the overall type I error rate is approximately 7%. In reality however, these hypotheses are strongly correlated. Thus, the overall type I error rate is bounded below by 2.5% and above by 7%.

R code for the power calculations is available at:

<https://gist.github.com/anddis/fc1a265d102b509b0eacd59ab065661a>

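### The stated 50–90% power for Strategy 6 vs 3 is more favourable than the SAP's own table, which runs from 48% to 87% under a conservative overlap assumption and does not by itself support calling the power sufficient

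*Combined protocol and SAP*

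**What the plan says.** In the SAP, under the updated sample size calculations of 2019, the first listed result is "50–90% power for the contrast S3M+TBx+SBx versus PSA+TBx+SBx". The assumptions given are:

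- "0.015–0.03 probability of detecting" ISUP ≥2 together with a positive PSA test;
- "0.57–0.63 TPF for the PSA test";
- a true relative TPF of 1 for Stockholm3 against PSA;
- "and a conservative DDR estimate";
- a ratio margin of 0.78, "and alpha to 0.025";
- about 7500 men in the experimental arm, reduced to 6000 by 20% drop-out.

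A table of 16 scenarios follows. Its lowest entry is 0.48 (detection rate 0.015, TPF 0.57). Its highest is the last row, "0.030 | 0.63 | 0.87".

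The section then says that this contrast determines the required sample size and that the study was powered to have "sufficient statistical power to answer comparisons of Stockholm3 vs. PSA within the experimental arm". It gives no numeric target for the contrast. Near its start, it explains that the final size balances time and money against power for Strategy 6 vs 3, and that different assumptions require different sizes. The only numeric power target in the SAP is 80%, in the March 2017 calculation for Strategy 6 vs 1.

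**The concern.** The summary sentence and the table describe the same calculation, and the sentence is the more favourable at both ends. A reader who takes only the sentence would believe that some of the assumed scenarios give 90% power and that none falls below 50%. Neither is true of the table.

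The word sufficient compounds this. It is attached to the contrast that justified enlarging the trial, without a target or a scenario regarded as most plausible. If the 80% used elsewhere in the SAP is the yardstick, 12 of the 16 printed scenarios fall short. Strategy 6 vs 3 is one of the two contrasts reported in Publication 2, so its stated power is likely to be cited when that result is interpreted.

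**Working it through.** **Inputs.** From the updated sample size section: N = 6000 analysable men; detection rate DR = 0.015, 0.020, 0.025, 0.030; TPF of PSA = 0.57, 0.59, 0.61, 0.63; true rTPF = 1; margin 0.78, so −log(0.78) = 0.2485; alpha 0.025 one-sided, so z = 1.96. The variance of log rTPF comes from the SAP section on contrasts within study arm: (b + c)/((a + b)(a + c)).

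**One assumption.** The section calls its overlap estimate conservative but does not print it. I took the smallest overlap that the two TPFs allow. With both equal to TPF, at least 2·TPF − 1 of all cancers are positive on both tests. As a share of PSA-positive cancers this is (2·TPF − 1)/TPF, which is 0.246 at TPF 0.57 and 0.413 at TPF 0.63.

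**Formulas.** Cancers positive on PSA: C = a + c = N·DR. Since rTPF = 1, a + b = C. Then a = C·(2·TPF − 1)/TPF, b + c = 2(C − a), SE = √(b + c)/C, and power = Φ(0.2485/SE − 1.96).

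**Lowest cell.** DR 0.015, TPF 0.57: C = 90, a = 22.1, b + c = 135.8, SE = 0.1295. Power = Φ(−0.041) = 0.484. Printed: 0.48.

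**Highest cell.** DR 0.030, TPF 0.63: C = 180, a = 74.3, b + c = 211.4, SE = 0.0808. Power = Φ(1.116) = 0.868. Printed: 0.87.

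**All cells, recomputed (printed):**

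| DR | TPF 0.57 | TPF 0.59 | TPF 0.61 | TPF 0.63 |
|---|---|---|---|---|
| 0.015 | 0.484 (0.48) | 0.516 (0.52) | 0.550 (0.55) | 0.585 (0.59) |
| 0.020 | 0.601 (0.60) | 0.636 (0.64) | 0.673 (0.67) | 0.709 (0.71) |
| 0.025 | 0.698 (0.70) | 0.733 (0.73) | 0.768 (0.77) | 0.802 (0.80) |
| 0.030 | 0.774 (0.77) | 0.807 (0.81) | 0.838 (0.84) | 0.868 (0.87) |

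The largest difference is 0.5 percentage points, so all 16 cells agree to rounding. Two alternatives do not reproduce the table: a two-sided alpha of 0.025 gives 0.37 and 0.80 at the two corners, and N = 7500 without drop-out gives 0.57 and 0.93. This supports both the minimum-overlap reading and the one-sided test with N = 6000.

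**Reading the grid.** The range is 48.4% to 86.8%, with a mean of 69%. Four cells reach 80%: DR 0.030 with TPF 0.59, 0.61 or 0.63, and DR 0.025 with TPF 0.63. None reaches 90%.

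**Sensitivity to overlap (same N, margin and alpha):**

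| Overlap among cancers | Power range | Cells at or above 80% |
|---|---|---|
| Minimum (matches the SAP table) | 48–87% | 4 of 16 |
| Independent: share of PSA-positive cancers also Stockholm3-positive = TPF | 72–97% | 12 of 16 |
| 70% of PSA-positive cancers also Stockholm3-positive (my assumption) | 86–99% | 16 of 16 |

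**The case against.** The strongest reply is that nothing has been miscalculated or concealed. To the nearest ten, 48 and 87 are 50 and 90, and the full table stands beside the sentence. The section says openly that the size is a compromise and that the overlap estimate is conservative. All of this stands, and it limits the point to wording.

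A reader might infer more from the table. The documents do not support these stronger readings:

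- **That the trial missed its power target.** The SAP sets no 80% target for Strategy 6 vs 3. The 80% belongs to the original Strategy 6 vs 1 calculation, so it is a yardstick here and not a broken commitment.
- **That the design has a 13–52% chance of missing true equality.** Those figures are one minus the table's extremes, and so are worst cases with respect to overlap. PSA is itself a component of the Stockholm3 test, which makes overlap below independence look unlikely.
- **That power is centrally about 67–78%.** This follows from 13% PSA-positive × 18% ISUP ≥2 = 2.3%. But the 18% comes from systematic biopsy, and Strategy 6 vs 3 lies wholly in the MRI arm. With the SAP's own uplift of 1.3, the detection rate is 2.34% × 1.3 = 3.0%, where the table gives 0.77–0.87. The SAP names no central scenario.
- **That a failed test would be read as inferiority.** The SAP never defines it so, and it already commits to reporting two-sided 95% intervals.

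The absence of a power figure for the within-arm ISUP 1 test is a separate matter of detail and not part of this inconsistency.

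**Conclusion.** The point holds as a minor correction. The stated 50–90% should read 48–87%: 2 points lower at the bottom and 3 at the top. Under the printed assumptions no scenario gives 90% power and 4 of 16 give at least 80%, so the grid alone does not support the unqualified claim of sufficient power.

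The conclusion about the range needs no assumption beyond the printed table. Calling the grid a lower bound rests on the minimum-overlap reading, which the SAP does not spell out but which the agreement of all 16 cells supports. It is a lower bound with respect to overlap only, for the given detection rate, TPF, N = 6000 and a true rTPF of 1. A true rTPF below 1 would reduce power. The finding does not show that the calculation is wrong or that the study is too small.

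**What to change.** In the updated sample size section:

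1. Replace the 50–90% statement with: *48–87% for non-inferiority on ISUP ≥2 under the conservative (minimum-overlap) assumption; at least 80% in 4 of 16 scenarios.*
2. Either delete the word sufficient at both places where the section applies it to this contrast, or tie it to a stated target power and overlap assumption. If the sponsor thinks greater overlap is plausible, the SAP can say so and print the result; independent overlap, for example, gives about 72–97%.

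The cost is a few words in the SAP and a slightly less favourable headline figure. Sample size, test, margin and decision rule are unchanged.

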Publication 2 will report the contrasts of Strategy 6 vs. 3 (S3M+TBx+SBx vs. PSA+TBx+SBx) and Strategy 6 vs. 1 (S3M+TBx+SBx vs. PSA+SBx), where the latter contrast corresponds to assessing the performance of the entire diagnostic chain of using Stockholm3 test to select men for further workup using MRI followed by targeted biopsies and systematic biopsies compared to using PSA followed by systematic biopsies (i.e. testing the overarching primary hypothesis of the trial). Sensitivity analyses will include contrast of Strategy 5 vs. 2 and Strategy 5 vs. 1. In addition, for the contrast of Strategy 6 vs. 1, we will – if Stockholm3  $\geq 11\%$  is more sensitive than PSA  $\geq 3$  – also report results at the operating point of Stockholm3 (i.e. the Stockholm3 cutoff) that gives equal sensitivity as PSA  $\geq 3$  within the experimental arm (analogously to how we performed the STHLM3 trial, see Grönberg et al.), see the “Additional analysis” section in this document for more information.

This comparison is motivated by the fact that MRI+targeted biopsy will be used more and more frequently, with the possibility of them eventually replacing systematic biopsies as the de-facto standard diagnostic tool. For example, the National Institute for Health Care and Excellence (NICE) in the UK already recommends MRI as “the first-line investigation for people with suspected clinically localised prostate cancer”. Therefore, we aim to compare the Stockholm3 test with the PSA test – in terms of sensitivity (ISUP $\geq 2$ ), specificity (ISUP1), number of biopsies and number of MRI scans – as a tool to select men for further workup, as well as compare the entire diagnostic chain of using Stockholm3 followed by MRI and TBx+SBx to the traditional diagnostic chain of using PSA followed by SBx (for which there exists level 1 evidence of reduced prostate cancer specific mortality when used for prostate cancer screening (Schröder et al. 2009 and 2014)). Publication 2 will cover the primary overarching hypothesis, as well as additional hypotheses 3 and 4.

Another way to motivate the order of these two publications is that the first publication will assess whether MRI and TBx+SBx improves diagnostic accuracy in a population based

 As also pointed out in by [name] and [name] in the review of the study protocol [Nordström et al, BMJ Open 2019]. The comments are now available at the journal's website.

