#### *Contrasts between study arms (unpaired design)*

Analyses will compare the difference in detection probabilities (DPs) between study arms. The DP is the probability of being endpoint-positive given the study arm and, possibly, either or both screening tests being positive. For example the DP of ISUP1 in men randomised to the experimental arm and Stockholm3-positive is equal to  $\Pr(\text{ISUP1} \mid \text{Stockholm3} \geq 11\%, \text{Experimental arm})$ .

**Absolute scale.** The absolute difference in DPs is defined as the DP in the experimental arm minus the DP in the standard arm ( $\Delta\text{DP} = \text{DP}_{\text{Exp}} - \text{DP}_{\text{Std}}$ ) or vice versa, as appropriate. It is estimated by plugging into the formula the observed proportions. An approximate 100(1- $\alpha$ )% two-sided Wald confidence interval for  $\Delta\text{DP}$  is calculated as

$$\widehat{\Delta\text{DP}} \pm z_{\alpha/2} \sqrt{\frac{\widehat{\text{DP}}_{\text{Exp}}(1-\widehat{\text{DP}}_{\text{Exp}})}{n_{\text{Exp}}} + \frac{\widehat{\text{DP}}_{\text{Std}}(1-\widehat{\text{DP}}_{\text{Std}})}{n_{\text{Std}}}}.$$

**Relative scale.** The relative difference in DPs is defined as the DP in the experimental arm divided by the DP in the standard arm ( $r\text{DP} = \text{DP}_{\text{Exp}}/\text{DP}_{\text{Std}}$ ) or vice versa, as appropriate. It is estimated by plugging into the formula the observed proportions. An approximate 100(1- $\alpha$ )% two-sided Wald confidence interval for  $r\text{DP}$  is calculated as

$$\exp\left(\log(\widehat{r\text{DP}}) \pm z_{\alpha/2} \sqrt{\frac{1}{\widehat{\text{DP}}_{\text{Exp}} * n_{\text{Exp}}} - \frac{1}{n_{\text{Exp}}} + \frac{1}{\widehat{\text{DP}}_{\text{Std}} * n_{\text{Std}}} - \frac{1}{n_{\text{Std}}}}\right).$$

Contrasts 3 vs 1, 2 vs 1, and 9 vs 7 will be analysed using absolute differences (Study 1). Contrasts 6 vs 1, and 5 vs 1 will be analysed using relative differences (Study 2).

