#### *Non-inferiority and superiority tests*

The null and the alternative hypothesis for a non-inferiority test for the  $\Delta DP$  are:

$$\begin{aligned} H_0: \Delta DP &\leq -\delta \\ H_a: \Delta DP &> -\delta \end{aligned}$$

where  $\delta > 0$  is the non-inferiority margin. This means that non-inferiority for a specific endpoint will be claimed if the lower boundary of the two-sided  $(2\alpha \times 100)\%$  confidence interval for the  $\Delta DP$  does not cover  $-\delta$ .

The null and the alternative hypothesis for a superiority test for the  $\Delta DP$  are:

$$\begin{aligned} H_0: \Delta DP &\leq \theta \\ H_a: \Delta DP &> \theta \end{aligned}$$

where  $\theta \geq 0$  is the superiority margin. This means that superiority for a specific endpoint will be claimed if the lower boundary of the two-sided  $(2\alpha \times 100)\%$  confidence interval for the  $\Delta DP$  does not cover  $\theta$ .

For comparisons on a relative scale (rTPF), the null and the alternative hypothesis for non-inferiority and superiority tests are

$$H_0: rDP \leq \exp(-\delta)$$

$$H_a: rDP > \exp(-\delta)$$

and

$$\begin{aligned} H_0: rDP &\leq \exp(\theta) \\ H_a: rDP &> \exp(\theta) \end{aligned}$$

respectively, with non-inferiority and superiority margins equal to  $\delta > 0$  and  $\theta \geq 0$ .

One-sided p-values will be calculated based on the test considered (non-inferiority or superiority).

Switching from non-inferiority to superiority: if the two-sided  $(2(1 - \alpha) \times 100)\%$  confidence interval for  $\Delta DP$  (rTPF) not only lies entirely above the non-inferiority margin, but also above the superiority margin, superiority will be claimed at the same alpha-level set for the non-inferiority test. In this case, we will also calculate the p-value associated with a test for superiority.

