### Primary endpoints

Contrasts between study arms: we will assess the non-inferiority of the experimental arm versus the standard arm in detecting ISUP $\geq 2$  cancers ( $\delta = 0.04$  or  $\exp(-\delta) = 0.78$ , as appropriate). The  $\alpha$  level is set to 0.025. Two-sided 95% confidence intervals will be reported.

Contrasts within study arms: we will assess the non-inferiority of the Stockholm3 test versus PSA in detecting ISUP $\geq 2$  cancers ( $\exp(-\delta) = 0.78$ ) and the superiority of PSA versus the Stockholm3 test in detecting ISUP1 cancers (i.e. a lower proportion of ISUP1 cancer detected according to the Stockholm3 test) ( $\exp(-\theta) = 1$ ). The  $\alpha$  level is set to 0.025 for both tests. Two-sided 95% confidence intervals will be reported.

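### The SAP's 7% ceiling on overall type I error is not a true ceiling, and it covers one contrast although three main contrasts are tested

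*Combined protocol and SAP*

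**What the plan says.** The note in SAP, Updated sample size calculations (performed during Spring and Summer 2019), opens with "Note: no correction for multiple comparisons was made". It counts three tests, on the ISUP ≥2, ISUP 1 and biopsy endpoints, and says that each "has an approximate type I error rate of 2.5% if the corresponding null hypothesis is true". It gives about 7% for the three together if they are independent. It then observes that the hypotheses are strongly correlated and concludes that "the overall type I error rate is bounded below by 2.5% and above by 7" per cent.

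Other parts of the SAP fix how many contrasts are tested:

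- Publications strategy of main study results: the primary contrast of Publication 1 is Strategy 3 vs 1. Publication 2 reports 6 vs 3 and 6 vs 1. Strategy 2 vs 1 is an additional analysis, and "Sensitivity analyses will include contrast of Strategy 5 vs. 2 and Strategy 5 vs. 1".
- Contrasts between study arms (unpaired design): lists 3 vs 1, 2 vs 1, 9 vs 7, 6 vs 1 and 5 vs 1.
- Primary endpoints and Key secondary endpoints (Statistical analysis): alpha is 0.025 for the between-arm tests. For the within-arm tests of ISUP ≥2 and ISUP 1, the α "level is set to 0.025 for both tests". The 2.5% for the biopsy test appears only in the multiplicity note.
- Overarching primary hypothesis and Primary aim: these name 6 vs 1, but no section ties the error rate, an alpha split or a testing order to that choice.

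**The concern.** A numerical upper bound on type I error is a property that readers will rely on. This one raises two doubts.

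First, the step from strong correlation to a 7% maximum holds only if the dependence lowers the chance of at least one false claim. Positive correlation does that, but negative correlation can raise it, and the note gives no sign. There is a plain reason to expect one negative pair. If by chance more men are biopsied in the experimental arm, more ISUP ≥2 cancers are found, which helps non-inferiority, while the reduction in biopsies becomes harder to show.

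Second, the word overall suggests the trial, but the three tests counted belong to a single contrast. With three contrasts reported as main results, the chance of at least one false claim among them is not limited by a figure computed for one.

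**Working it through.** **Inputs.** One-sided α = 0.025 per test (SAP, Primary endpoints, Key secondary endpoints and the multiplicity note). Three tests per contrast (multiplicity note). Three main contrasts (Publications strategy). No correction (multiplicity note).

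**Step 1: the SAP's own figure.** With k independent tests, all nulls true at their boundary, the error is 1 − (1 − α)^k. For k = 3: 1 − 0.975³ = 0.0731. To the whole per cent this is the SAP's 7%, so the figure is reproduced as a rounded independence value.

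**Step 2: the bound under any dependence.** The sum of the individual rates is 3 × 0.025 = 0.075. The excess over the stated ceiling is 7.5 − 7 = 0.5 points.

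**Step 3: sign of the correlations.** One between-arm contrast was simulated at the null boundary.

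- From the documents: about 1,600 men with PSA ≥3, split 2:3 into 640 and 960; a 4-point margin.
- Control ISUP ≥2 rate: 18% (SAP) with 80% of men biopsied, or 14.4% (assumed; 0.8 × 18%) with 60% biopsied (assumed).
- Assumed: ISUP 1 rate of 12% to 30%.

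| Pair of tests | Correlation |
|---|---|
| ISUP ≥2 non-inferiority and biopsy reduction | −0.22 to −0.32 |
| ISUP ≥2 non-inferiority and ISUP 1 reduction | 0.14 to 0.29 |
| ISUP 1 reduction and biopsy reduction | 0.18 to 0.53 |

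The chance of at least one false claim was 7.1% to 7.4%. The individual Wald tests ran at 2.3% to 2.8%, so the second digit should not be over-read. The signs are mixed, and the result is close to the independence value.

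**Step 4: three main contrasts.** 3 × 3 = 9 tests.

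- If independent: 1 − 0.975⁹ = 0.204.
- Under any dependence: at most 9 × 0.025 = 0.225.

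**Step 5: allowing for shared men.** The three contrasts were simulated together.

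- From the documents: about 2,100 randomised men, split 2:3 into 840 and 1,260; 80% biopsied, from the 20% drop-out.
- Assumed: ISUP 1 in 15%; ISUP ≥2 in 22% of men positive on both tests and 10% of men positive on one; each one-test-only group 21% or 30% of randomised men.
- The 21% setting makes 58% + 21% = 79% of men PSA-positive, close to the SAP's 13/16.5 = 78.8%.
- All contrasts were put on the ratio scale with margin 0.78, although the SAP analyses 3 vs 1 on the absolute scale. The two margins nearly agree: 0.14/0.18 = 0.778.

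On the ratio scale, 6 vs 1 equals 3 vs 1 times 6 vs 3, so the three ISUP ≥2 nulls cannot all sit at their boundary together. The simulation put 3 vs 1 and 6 vs 1 at 0.78, which makes 6 vs 3 equal to 1 and leaves eight true nulls. The chance of at least one false claim was 14.5% and 14.8% in the two settings. The 22.5% ceiling is therefore valid but loose.

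Against the stated 7%: 14.5/7 = 2.1 and 14.8/7 = 2.1.

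**The case against.** The best defence is that the SAP hides nothing. It says that no correction is made, names the three tests and conditions on those three nulls, so a careful reader could take the range as applying to one contrast. That stands against any suggestion of concealment. It does not rescue the number, because the note calls the rate overall, gives it an upper limit, and does not confine it to one contrast.

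It can also be said that 6 vs 1 is the primary hypothesis and the rest is secondary. If 6 vs 1 were declared the only confirmatory contrast, the inflation across contrasts would concern secondary claims only. But the note does not say so. The two power statements just before it concern 6 vs 3 and 3 vs 1, and Publication 1 has its own primary contrast.

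A third argument is that the primary hypothesis joins non-inferior sensitivity and superior specificity. If success required every component, the error for that joint claim would be at most 2.5%. The note does not adopt that rule and treats the tests as separate claims.

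A reader might go further and count all seven named contrasts: 21 tests, 1 − 0.975²¹ = 41.2% if independent and at most 52.5%. The documents do not support this as a headline. They label 2 vs 1 an additional analysis and 5 vs 1 and 5 vs 2 sensitivity analyses, and they do not name 9 vs 7 in the publication strategy. The labels are not fully consistent, since 5 vs 1 is also key secondary aim 4, but the nine-test figure does not depend on it.

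**Conclusion.** The stated ceiling is wrong as written, in two ways of unequal weight. Within one contrast the valid bound is 7.5%, provided each test holds its nominal 2.5%. The excess is at most 0.5 points and would hardly matter alone. Across the three main contrasts the bound is 22.5%, the independence value is 20.4%, and about 15% is realistic under the simulation's assumptions, which is roughly twice the stated 7%.

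A reader might infer a threefold inflation. That follows only from the independence or worst-case values (20.4/7 = 2.9; 22.5/7 = 3.2), and the contrasts share men. The lower limit of 2.5% is correct when at least one null is true at its boundary.

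Neither 20.4% nor 22.5% counts everything. Key secondary aim 3 also tests for fewer MRI examinations in 6 vs 3, and Study populations has every analysis reported in both the ITT and PP populations without saying which decides.

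**What to change.** Replace the sentence that gives the 2.5% to 7% range with:

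> Within a single contrast, the type I error over the three tests (ISUP ≥2, ISUP 1, biopsy) is at most 7.5% under any dependence. This does not cover the trial as a whole. Over the three main contrasts (3 vs 1, 6 vs 3, 6 vs 1) on these endpoints it is at most 22.5%, and no correction is made. Any further tests, such as MRI examinations in 6 vs 3, add to this.

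This costs only wording and changes no analysis.

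Testing in a fixed order within each contrast, with ISUP ≥2 non-inferiority first, is an option rather than a requirement. In one analysis population it would hold each contrast at 2.5%. The primary hypothesis joins its components without ordering them, so the order would be a new rule. It has a price: if non-inferiority fails, the later tests in that contrast become descriptive. It would also have to be set before any comparative analysis, in line with the SAP's Preface. If that point has passed, restate the bound only.
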